### Goal Attainment Scaling (GAS)

The GAS is an individualized, criterion-referenced outcome measure that is sensitive to change and well established within pediatric rehabilitation [36, 60]. The procedure involves describing the baseline level of performance and specifying a range of possible outcomes for each goal. The scale comprises five levels, ranging from −2 to +2, where −2 represents baseline performance, 0: expected level of goal achievement and +2: performance substantially exceeding the expected goal. Ratings of goal attainment are aggregated and converted into an overall T-score. A T-score of 50 represents achievement of the expected goal (level 0) and denotes a clinically meaningful improvement. T-scores derived post-intervention and at follow-up were used for analysis. Parents will video-record the goals, before and after the intervention period.

### Heart rate measures

Heart rate monitoring (Polar, Kempele, Finland) provides an objective measure for describing the intensity of physical activity. These are non-invasive and are worn with a band around the upper arm or the wrist. The children wear the heart rate monitors during the training sessions, and the accelerometers at home to estimate daily physical activity.

### Questionnaires

Prime-P: The Pediatric Rehabilitation Intervention Measure of Engagement – Parent version (PRIME-P) [61] is a self-report measure. The questions are about what parents thought, how they felt, and what they did during their child’s therapy session and how the session has affected their overall feelings about the intervention process.

PrimeSP: The Pediatric Rehabilitation Intervention Measure of Engagement - Service Provider version (PRIME-SP) captures therapists´ observations of client engagement in an intervention session, with engagement defined as active involvement and investment in the client role [62]. The PRIME-SP has three parts - an overall rating of engagement, ratings of aspects of engagement (affective, cognitive, and behavioural involvement), and a place to record observations of factors that may have influenced client engagement.

An electronic diary: To ensure sufficient training intensity, parents were asked to document the daily duration of goal-related practice and Frame running. An electronic form will be sent out once a week during the training period. Parents will be asked to summarize the training time and answer a few questions about feasibility.

### Evaluation of the treatment

Following completion of the study period, participants will be invited to complete an electronic evaluation questionnaire. The questionnaire comprises 20 questions assessing participants’ experiences of study participation, perceptions of the project organization, the feasibility of conducting training both at home and in group-based sessions, and the adequacy of the support provided.

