**Method:**

The study uses a prospective repeated-measures intervention design with assessments conducted during baseline, intervention, and post-intervention follow-up phases. At least 18 children meeting the inclusion criteria (CP diagnosis, age 2–5 years, GMFCS II–IV) will participate. The design consists of three baseline measurements, a 12-week intervention phase and three post-intervention measurements, across approximately 5–6 months. The program combines home-based training and hospital-based group training, with parents as active trainers and therapists providing coaching. Frame Running and goal-directed training are tailored to individual goals, set collaboratively with families. Outcome measures include the Gross Motor Function Measure (GMFM-66), Functional Mobility Scale (FMS), Paediatric Evaluation of Disability Inventory Computerised Assessment Test (PEDI-CAT), time-based mobility tests: ultrasound assessment of muscle size and morphology, gait analysis, accelerometry (7-day activity monitoring), heart rate monitoring during training, and Goal Attainment Scaling (GAS). Feasibility and fidelity will be investigated by questionnaires.

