To promote sufficient intensity and practice dosage, training is implemented across two complementary settings: home-based training and hospital-based group sessions. Parents play an active and central role in both contexts. During group sessions, trainers integrate all elements of the F-words framework—fostering social relationships, enhancing fitness, promoting enjoyment, engaging families, and cultivating optimism for future participation [26]. Group-based activities also enable children and families to learn from peers and experience the motivational benefits of social interaction, which enhances engagement and supports the long-term sustainability of physical activity participation. Although the intensity achieved through this combined approach can be questioned, it is supported by previous studies using similar designs [37, 38]. There is also evidence that, when appropriately supported, parents can deliver high-frequency, intensive training in the child’s natural environment, consistent with the principles of family-centered practice [39, 40]. Overall, this approach requires a substantial commitment from families, particularly given the young age of the children. However, embedding training within everyday routines is expected to facilitate a high number of repetitions and thereby provide an intensity of practice sufficient to effect the motor outcomes.

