### Trial design

The study uses a prospective repeated-measures intervention design with assessments conducted during baseline, intervention, and post-intervention follow-up phases. There will be three baseline measurements, a 12-week intervention phase, and three post-intervention measurements (Fig. 1 and Table 1). Primary clinical outcomes are assessed during the baseline and follow-up phases, while process-related measures, see Table 1. The total study period is approximately 5–6 months.

**Table 1 Tab1:** Assessments to be collected during the training period, B=Baseline, F=Follow up

Assessments	B1	B2	B3	F1	F2	F3
GMFM-66	X	X	X	X	X	X
Funtional Mobility Scale	X	X	X	X	X	X
Time Up and Go	X	X	X	X	X	X
pROM and tonus/MAS		X		X		
Walking/running, 10 m	X	X	X	X	X	X
Frame Running 30 m	X	X	X	X	X	X
Ultra sound	X		X	X		
Gait analysis		X		X		
Pedi-cat, mobility	X	X	X	X	X	X
Prime P/SP	X		X	X		
Accelerometry	X		X	X		X
Goa Attainment Scale			X	X		X
Parent Evaluation						X

This design is informed by principles from single-subject research designs, particularly the use of repeated baseline measurements to characterize within-participant variability before the intervention. However, we do not expect children to return to baseline when the intervention is withdrawn. The planned sample size of at least 18 participants allows also for both individual-level and group-level analyses. This is an advantage when working with heterogeneous populations, such as children with CP, where variability in the magnitude and direction of response to treatment may obscure results in randomized controlled trials (RCTs) [44]. Repeated measurements across phases also allow exploration of individual response patterns and to investigate whether participant characteristics are associated with differential responses to the intervention. Although participants and therapists cannot be blinded to the intervention, outcome assessments are conducted by independent assessors with no involvement in the training phase.

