### Statistical method

Demographic and clinical characteristics of the participating children and parents will be summarized using descriptive statistics. Continuous variables will be presented as means and standard deviations or medians and interquartile ranges, as appropriate, while categorical variables will be presented as frequencies and percentages.

Outcome data will be analyzed at both the individual and group levels. At the individual level, graphical displays will be used to visualize changes over time for each participant across study phases. Visual inspection will focus on changes in level, trend, and variability between baseline and follow-up measurements. These graphical analyses will be used to complement the quantitative analyses and to explore individual response patterns. At the group level, outcome measures obtained at baseline and post-intervention follow-up will be compared using appropriate repeated-measures statistical methods. Depending on the distribution and characteristics of the data, analyses may include paired t-tests or non-parametric alternatives such as the Wilcoxon signed-rank test. Effect sizes (e.g., Cohen’s d or equivalent non-parametric effect size measures) will be calculated and reported to facilitate interpretation of the magnitude of change. Given the limited number of observations within each phase, formal assessment of autocorrelation is not expected to provide reliable estimates. Results will therefore be interpreted with consideration of the dependency inherent in repeated measurements obtained from the same participant and in conjunction with graphical inspection of individual trajectories. In cases where graphical and statistical findings diverge, results will be interpreted cautiously.

Missing data will be described for each outcome measure and study phase. The number and proportion of missing observations will be reported together with reasons for missingness when available. Given the limited number of repeated measurements within each phase, missing values will not be imputed. Analyses will be based on available data, and the potential impact of missing observations on the interpretation of findings will be considered when reporting the results. Participant withdrawal and missed assessments will be reported separately.

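### The overall parent evaluation is scheduled once, after the study period, with none described at withdrawal, so its feasibility results may mainly represent families who complete

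*Protocol article*

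**What the plan says.** Feasibility is a stated question. The abstract says "Feasibility and fidelity will be investigated by questionnaires", and the Discussion names feasibility among the things the study is expected to inform.

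Two parent-completed instruments are described as covering it:

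- **The end-of-study evaluation** (Evaluation of the treatment). The timing is: "Following completion of the study period, participants will be invited to complete an electronic evaluation questionnaire". It has 20 questions. Besides the experience of taking part and the project organisation, it covers "the feasibility of conducting training both at home and in group-based sessions, and the adequacy of the support provided". In Table 1 (Trial design) the row "Parent Evaluation" has one mark, in the last column, F3.
- **The weekly electronic diary** (Questionnaires). On frequency, the section says "An electronic form will be sent out once a week during the training period", and Table 2 marks the diary in each of weeks 1 to 12. On content, it says "Parents will be asked to summarize the training time and answer a few questions about feasibility".

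On missing data, Statistical method says "Analyses will be based on available data", without imputation. The same paragraph commits to reporting withdrawals and missed assessments, with reasons for missing data where they are known. Fidelity adds attendance records, and Safety and ethics adds documentation of adverse events throughout the study.

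**The concern.** The one form that asks a family for an overall judgement of home training, group training and support is tied to the end of the study. A family that leaves during training or follow-up has no scheduled occasion to complete it.

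Leaving could well be related to what the form measures. The section on the programme framework says "this approach requires a substantial commitment from families, particularly given the young age of the children". The programme asks for daily parent-delivered practice, a weekly 90-minute hospital session and transport of the Frame Runner. Safety and ethics lists falls, collisions, fatigue and overexertion as risks.

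If families who find the programme hard to sustain are under-represented among respondents, the summary describes mainly those who could sustain it. The views most useful for redesign would also be missing, and they are hard to recover once a family has left. What is at stake is the feasibility conclusion. The analysis of the GMFM-66 and the other outcome measures is not affected by the timing of this form.

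**Working it through.** **Step 1. Is the timing stated or merely omitted?** It is stated. The text places the form after the study period and Table 1 places it at F3. The two agree, so this is a fixed schedule and not a detail left out of a condensed article. What the article does not say is whether families who have withdrawn are also invited.

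**Step 2. What reaches a family that stops early?**

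| Source | Until when | What it gives |
|---|---|---|
| Weekly diary | Until the family stops, at latest week 12 | Training time and some feasibility questions, content not listed |
| Attendance records | While attending group sessions | Adherence and dose |
| Adverse event documentation | Throughout the study | Incidents |
| Withdrawal reporting | At analysis | Numbers, and reasons where known |
| 20-question evaluation | F3 only | Overall view of home training, group training, organisation and support |

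A family that stops in week 6 has been sent about six diary forms. One that leaves between F1 and F3 has been sent all twelve. Neither has a scheduled point for the last row, and no other row is described as collecting an overall view of burden and support.

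**Step 3. How large could the effect be?** The planned number is 3 groups × 6 children = 18, which matches the stated minimum. The article gives no dropout rate and defines no yes/no feasibility response or threshold, so everything below is assumption.

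Let d of 18 families withdraw unasked, let all completers respond, and let p be the proportion of completers who rate the programme favourably.

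- Worst case, all withdrawers unfavourable: proportion among all enrolled = p(18 − d)/18.
- Overstatement = p − p(18 − d)/18 = p·d/18.

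| d | Overstatement, p = 0.80 | Overstatement, p = 1.00 |
|---|---|---|
| 0 | 0 | 0 |
| 1 | 0.80 × 1/18 = 4.4 points | 1/18 = 5.6 points |
| 3 | 0.80 × 3/18 = 13.3 points | 3/18 = 16.7 points |
| 4 | 0.80 × 4/18 = 17.8 points | 4/18 = 22.2 points |
| 6 | 0.80 × 6/18 = 26.7 points | 6/18 = 33.3 points |

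The direction is not forced either. With d = 3 and 12 of 15 completers favourable (80%), the proportion among all enrolled lies between 12/18 = 67%, if all three withdrawers were unfavourable, and (12 + 3)/18 = 83%, if all three were favourable. The table is therefore an upper bound under a chosen scenario and does not estimate the bias. It largely restates the assumed number of withdrawals.

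**The case against.** A reader might infer that families who stop because of burden, distress or injury are never asked about feasibility, and that feasibility will therefore certainly look better than it is. The documents do not support either statement. The diary asks about feasibility every week until a family stops. Withdrawals are to be reported, with reasons where known, and attendance and adverse events are recorded, so such families are not hidden. Whether the evaluation flatters the programme depends on how many withdraw, whether they are invited anyway and how feasibility is summarised. None of these is given.

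Other points on this side are fair. The article does not rank the 20-question form above the diary, and the abstract speaks of questionnaires in the plural. The invitation is addressed to participants and is not expressly limited to completers, and an electronic form needs no visit. The fuller protocol, not shown, may cover withdrawn families. Feasibility is descriptive here, since the stated objectives are mobility and physical activity.

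These arguments limit the point without removing it. The schedule that is stated has one occasion, at the end. The diary ceases when the family stops and is not described as asking why. Attendance and adverse event records do not carry a parent's view of burden or support, and no procedure for collecting reasons for withdrawal is described. Even if withdrawn families were invited after the study period, a family that left early in training would be asked only after a long delay.

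**Conclusion.** The point holds in a limited form. The broadest parent-reported feasibility instrument described is scheduled once, after the study period, and no administration at withdrawal is described. Its results may therefore represent mainly completers and may lean favourable. Calling it the broadest is a reading of the listed content and not the article's own label.

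The effect is nil if nobody withdraws and otherwise of unknown size. The worst case of about 4 to 6 percentage points per withdrawn family rests on four assumptions: 18 enrolled families, all completers responding, 80% to 100% of them favourable, and every withdrawer both unasked and unfavourable.

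This is a modest weakness in the feasibility evidence, worth correcting because the change is small and the information is hard to obtain later.

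**What to change.** - Send the same electronic questionnaire at F3 or at withdrawal, whichever comes first.
- Add one voluntary item on the main reason for stopping, for example burden, distress or fatigue, injury or pain, illness, or other.
- Report the number responding out of all enrolled families, and show completers and withdrawers separately.
- Present these results beside the weekly diary feasibility items and the withdrawal counts, so that the sources can be read together.

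The cost is one additional REDCap trigger and one item, and parents already complete forms in REDCap. Some withdrawing families will not answer, so the gap will narrow but may not close, and the reported feasibility may come out slightly lower.

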### Fidelity

Intervention fidelity will be examined at several time points during the trial to assess how closely the *Full Speed Ahead* program is delivered according to its intended design. Fidelity will be described in terms of adherence, dose, quality of delivery, and participant engagement [63].

Adherence to the intervention protocol and training dose will be monitored using attendance records from group sessions and weekly training diaries completed by parents. Quality of delivery will be evaluated using the PRIME-O, which captures therapists’ engagement, attitudes, and use of coaching strategies during the intervention. Child engagement will be assessed using the PRIME-P, in which parents rate their child’s engagement; these measures will be collected repeatedly during both the assessment and training phases. In addition, therapists will rate engagement during group training sessions by PRIME-SP. Physiological measures, including heart rate monitoring and accelerometer data, are outcome measures but will also be used as complementary indicators of fidelity, reflecting the intensity and amount of physical activity delivered.

### Safety and ethics

Frame Running can be performed at high speeds and therefore carries a risk of falls and collisions with other people or surrounding objects. An information sheet on risk factors has been prepared and will be given to the families. To mitigate these risks, children will be required to wear a helmet during Frame Running, the training area will be kept clear of obstacles not included in the program, and a designated adult (parent and/or therapist) will always remain close to the child. In addition, because the intervention aims to promote moderate- to high-intensity exercise, there is a potential risk of fatigue and overexertion, particularly in children who are not accustomed to vigorous activity. Trainers will therefore monitor the child’s tolerance during each session, adapt the intensity, provide rest breaks when needed, and stop the activity if safety concerns arise. Participation is voluntary, and the child’s interests will be respected throughout. As young children may have limited ability to articulate discomfort, therapists will actively attend to behavioural cues (e.g., distress, withdrawal, pain behaviour, or marked fatigue and will pause or discontinue the session if the child does not wish to continue. The intervention is intended to be challenging yet enjoyable, and children will never be pressured to participate beyond their comfort or capability. All adverse events and other unexpected incidents will be documented throughout the study in accordance with a predefined adverse events procedure and reported as required, and parents will receive written safety information before the intervention starts.

## Discussion

The FSA program aims to address the need for effective interventions targeting gross motor function and health in young children with CP. Currently, there is a lack of evidence for effective training programs for this group of children [11, 64]. In particular, research evaluating interventions for non-ambulant children with CP is scarce; most existing studies have focused on children classified as GMFCS levels I to III, leaving those at levels IV and V underrepresented and often without access to evidence-based interventions [65].

By implementing a new early and intensive program, consisting of a combination of Frame Running and goal-directed training, the FSA program aims to facilitate higher levels of functioning and participation than would be expected without such intervention, both short and long term. If proven effective, this approach could have substantial implications for planning both short- and long-term treatment and support services for young children with CP.

The prospective repeated-measures intervention design allows detailed analysis of individual response patterns over time, while also supporting group-level analyses. This is an advantage, as the variation among children is considerable and prospective repeated-measures intervention design allows for a broad understanding of the intervention impact on each participant, supporting the development of more effective and personalized treatment strategies for children with CP.

This study has limitations. The prospective repeated-measures intervention design does not include randomization or a control group, which limits causal inference. Blinding is also limited, as participants and therapists cannot be blinded to the intervention, although independent assessors will perform outcome assessments whenever possible. In addition, the relatively small sample size and the heterogeneity of children with CP may limit generalizability. Variation in adherence to home-based training may also affect outcomes. However, repeated assessments across study phases and the combination of individual- and group-level analyses are expected to provide important information about the feasibility and potential effects of the intervention.

Despite these limitations, the study is expected to provide important knowledge about the feasibility and potential effects of an early, intensive, family-centered mobility intervention for young children with CP. The findings may help guide future intervention development and inform clinical practice for this underserved question.

## Data Availability

No datasets were generated or analysed during the current study.

## Abbreviations

CP: Cerebral palsy
FSA: Full Speed Ahead
pROM: passive range of motion
GAS: Goal Attainment Scaling
